#### 4.4. Coding Dictionaries

Coding of medical terms is performed by the Data Management department of YYY as described in the DMP, using internationally recognized and accepted dictionaries.

- The coding of adverse events is done using MedDRA.
- Medications are coded using the WHO-Drug Dictionary Enhanced (WHO-DDE).

The dictionary versions finally used for analysis will be indicated in the tables and listings.

#### 4.5. Final Data Review and Protocol Deviations

The primary purposes of a Blind Data Review Meeting (BDRM) are to discuss any statistical analysis issues and to finally review the protocol deviations detected among the randomized patients in order to classify them as minor (not relevant) or major (relevant impact on the evaluability). Each protocol deviation that may influence the results of the primary efficacy variable is rated as major. Taking the rating of protocol deviations into consideration, each patient is assigned to the corresponding analysis population (see Section 4.1).

After finishing the data cleaning process, a BDRM is arranged prior to locking the database. The conduct details of the BDRM, meeting participants and required data listings to be reviewed during the BDRM (and their suppliers) are detailed in a separate Data Review Plan.

Protocol deviations are identified during monitoring, the medical review process, the data cleaning process, or systematically by SAS programming performed by YYY. Protocol deviations are categorized with respect to: Inclusion and exclusion criteria, audiological measurements, laboratory, study drug administration, concomitant medication, visit date deviation, reporting of SAEs, GCP-relevant deviations, and other.

In addition, specific data listings are prepared for the BDRM in order to check for protocol deviations visually among the recorded medications.

Major protocol deviations include the following situations:

- Inacceptable deviation of the in- and exclusion criteria as assessed at the BDRM
- Premature unblinding of the patient's treatment allocation
- Substantial use of prohibited concomitant treatment as assessed at the BDRM
- Poor compliance to treatment or the study procedures as assessed at the BDRM
- Discontinuation of IMP due to missing fibrinogen on Day 2.

In addition, there may be other circumstances leading to exclusion from the PPS, as decided at the BDRM.

To summarize all decisions taken at the BDRM, a detailed meeting protocol will be written and signed. The BDRM meeting minutes will include a complete list of all rules and criteria on the identification and relevance assessment of actually arisen protocol deviations as agreed in the BDRM. All patients excluded from any analysis population will also be listed together with the reason for exclusion.

#### 4.6. General Presentation of Summaries and Analysis

All study data will be presented in individual patient data listings. Data will be sorted by treatment, patient number, and visit. Where appropriate, the listings will include derived variables as per Section 4.3.

Each statistical table will contain a reference to the related patient data listing.

All study variables will first be analyzed in a descriptive way. Descriptive statistics will be displayed by treatment group (and overall if applicable) as follows:

- Continuous variables will be described using the number of non-missing values, arithmetic mean, standard deviation, minimum value, median, and maximum value ('summary statistics')
- Categorical variables will be presented by the absolute frequency (n) and the relative percentage (%) for each observed modality, whereas missing values will be displayed as own category ('frequency table').

Statistical tables will show results for each treatment group. For baseline and background variables, an additional 'Overall' column will be included, but not for efficacy and safety variables.

In general, the analysis of safety data will be based on the Safety set (SFS). The analysis of efficacy data will be based primarily on the Full analysis set (FAS), while alternative summary tables on efficacy variables will be done on the Per protocol set (PPS) as sensitivity analysis. Each analysis population will contain patients of both treatment groups in approximately a 2:1 ratio.

Usually, all patients within a given analysis population will be considered for analysis; descriptive by-visit analyses will be based upon only those patients who did not terminate the study prior to a given visit. Each table will display the total number of patients per treatment group (and overall, if applicable).

Further specifications regarding the layout of end-of-text tables and listings are given in Appendix 13.4 of this SAP. A list of all statistical tables and listings to be produced can be found in Appendices 13.2 and 13.3. These overviews also indicate the analysis population(s) for which a respective parameter will be evaluated. Moreover, the generation of mock TFLs is addressed in Section 13.7.

Any figures/graphics produced must be legible after been copied in black even if the original version is colored.

The layout of in-text tables for a subsequent report is covered in Appendix 13.6.

Raw SAS procedural outputs will be handed over to NORDMARK for the primary efficacy variable, as stated in Appendix 13.8.

#### 4.7. Statistical Software

All statistical analyses will be performed by programming using the software SAS® Version 9.3 or higher. (STATISTICAL ANALYSIS SYSTEM, SAS Institute, Cary, NC, USA).

### 5. Statistical/Analytical Issues

#### 5.1. General Considerations

Based on the raw database containing the recorded CRF data and on other data such as protocol deviations and central lab data, analysis data sets according to internal standards will be programmed that will be used for the generation of summary tables, figures and listings (TFLs). To meet common quality control requirements, the analysis of the following variables will be double-programmed by a second biostatistician:

- Change in PTA (Air) in the affected ear from Visit 1 to Visit 5 (including the corresponding analysis data set needed for the primary efficacy variable)
- Adverse event rates.

For all other TFLs, a second biostatistician will review the SAS program codes and will check the results for consistency at least visually. All SAS programs used for the evaluation will be stored in a study-specific directory on the YYY file server together with the corresponding 'list' and 'log' files.

Quantitative efficacy variables (including the primary efficacy variable) will be analyzed by means of an analysis of covariance (ANCOVA) based on the generalized linear model (SAS procedure PROC GLM). Underlying model assumptions, such as normality and homogeneity of variance, will be assessed at the BDRM. Should these assumptions be violated, appropriate data transformations or the choice of a non-parametric analysis method will be considered. These analyses will be performed for the primary efficacy variable in addition to the originally planned analysis.

For the primary efficacy variable, confirmative testing will be performed with the aim to show superiority in favor of the treatment with ancred over placebo. Basically, a two-sided 5 % significance level will apply. All other variables will be exploratively compared between treatment groups.

#### 5.2. Adjustments for Covariates

Besides the treatment group as fixed effect, the following covariates will be included in the ANCOVA models for quantitative efficacy variables:

- Study center (random effect)
- Baseline value (covariate).

The study center is employed in the statistical model to compensate for site effects leading to a high variance in endpoint values among centers, and the baseline value is included due to possible disease severity among patients.

#### 5.3. Handling of Dropouts and Missing Data

A screening failure is a patient having signed informed consent but discontinuing before being randomized. Such patients are not kept in the database.

Dropout patients are not explicitly referenced in the study protocol. However, the following definition is provided in this SAP:

- Patients randomized who either discontinue the study prematurely or are withdrawn from study by the investigator before the planned study termination are assessed as **dropouts**.

Dropout patients are not substituted. To compensate for dropouts, a 12 % dropout rate was used in the sample size determination.

Dropout patients will be evaluated like any other patient terminating the study regularly while accounting for missing data. The FAS includes dropout patients.

Missing values will usually be shown as missing in patient data listings. If there is the need to show data imputations, imputed values are flagged appropriately.

For the statistical analysis of efficacy variables, the LOCF (last observation carried forward) method will be applied to impute missing Visit 5 values, i.e, the baseline value will be carried forward. Missing values for Visit 6 or Visit 7 will not be replaced as these visits are far beyond treatment stop.

Regarding PTA, a missing PTA threshold value for a given frequency at Visit 5 is replaced by the respective preceding value available at Screening. Imputations will not use values of the other ear (left/right) or of the other conduction type (air/bone). If a baseline value for a given frequency is missing, the frequency will be excluded from statistical analysis of the respective patient.

Regarding the statistical evaluation of background and safety variables, missing values will not be replaced or imputed; they will be handled as missing by displaying an own category in frequency tables.

However, missing data, outliers and other spurious or implausible data are discussed in the BDRM prior to unblinding the database.

#### **5.4. Interim Analysis and Data Monitoring**

No data monitoring committee is established for this trial.

Although introduced by a protocol amendment, an interim analysis will not be performed.

#### **5.5. Multicenter Studies**

This study is conducted as a multicenter trial. The data of all centers will be combined for statistical analysis.

The study center will be used as covariate for statistical testing, see Section 5.2. In case of a large variability of enrolment at centers, study centers will be pooled according to external criteria (e.g., country, region, or investigator's experience). The exact pooling rule is established at the BDRM, before unblinding.

#### **5.6. Multiple Comparisons/Multiplicity**

As confirmative statistical testing will be done for the primary efficacy variable only, no p-value adjustments for multiple comparisons nor power adjustments are necessary. All p-values gained underlie the experiment-wise significance level without adjustment for a study-wide level.

#### **5.7. Examination of Subgroups**

The patient subgroups as defined in Section 4.2 will be evaluated descriptively for the following study variable:

- Change in PTA (Air) in the affected ear from Visit 1 to Visit 5 (see Section 9.1.1).

In addition, to assess the relevant risk factors, a step-down analysis of covariance (ANCOVA) model will be established on above study variable that initially includes the subgroups of Section

4.2 (but not subgroups based on quartiles and the subgroups for rescue medication use) and the following factors at Visit 1:

- Biomarkers (CD38+ and CD42+ cells, interleukin-6, TNF- $\alpha$ )
- Frequencies affected by SSSL (high-tone, low-tone, pantonal, unspecified)
- Diabetes mellitus (yes, no)
- Hypertension (yes, no)
- Ischemic heart disease (yes, no).

Diabetes mellitus, hypertension and ischemic heart disease will be identified during the BDRM based on the entries for physical examination at Visit 1.

In a first step, all variables with low influence ( $p > 0.5$ ) will be removed. From the resulting model, successively the factor with lowest influence will be eliminated until a model remains that contains only the significant influence factors ( $p < 0.05$ ).

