## 2. Changes from Protocol including Amendments

One interim analysis after 30 evaluable patients is planned in the study protocol. As it is expected that – due to expiration of available study medication – in total only a few more evaluable patients will be enrolled than planned for the interim analysis, the interim analysis is skipped. There will only be one final analysis of study data.

The study protocol defines only the Full analysis set for analysis of efficacy but requires in addition evaluability of patients in the sample size estimation. To address this, the Per protocol set is introduced in this SAP as secondary analysis population.

The study protocol states that qualitative parameters spread in very large contingency tables will be analyzed with the asymptotic chi-square-test, but as such data do not occur this test is not used in this SAP.

According to the study protocol, demographic and pre-treatment characteristics that are continuous should be analyzed by a general linear model (GLM) to determine comparability of the ancrod and placebo groups at baseline. If treatment group differences were seen at the 0.10 level of significance, these variables would be added as stratification variables or covariates to the efficacy analyses. As the study is randomized, it was decided to not follow this request and to not assess baseline differences.

The study protocol leaves open whether an analysis of covariance or a general linear model should be used to evaluate the primary efficacy variable and quantitative secondary efficacy variables. As the primary efficacy variable (change from Baseline) may be dependent on the baseline value, the baseline value should be taken into account for the primary analysis as covariate. For this reason, statistical evaluation will be performed using a generalized linear model, without prior investigation at the BDRM.

Introduced by several protocol amendments, various changes have been implemented in the CRF. However, the statistical analysis of patients being included in the study prior to an implemented CRF change is not affected, and values will be missing for added CRF parameters for all patients enrolled under a previous protocol amendment; a footnote for the respective summary tables will clarify the data issues referring to CRF amendments. In detail, the following changes relevant for the statistical analysis were made to the CRF:

- Exclusion criterion 17 was added with Amendment 4.1

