### 3.5. Sample Size Determination

Sample size determination for this study is based on 2-sided t-tests with a global alpha level of 5 % and a statistical power of 90 %. A standard deviation of 20 dB for the test statistic is assumed. In order to be able to confirm a treatment difference of 15 dB PTA of active treatment versus placebo with a 2:1 randomization, a total number of 87 evaluable patients will be required, 58 patients in the group receiving ancrod, and 29 patients receiving placebo. To compensate for dropouts, a total number of 99 patients is planned to be enrolled, 66 patients receiving ancrod, and 33 patients receiving placebo.

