### 4.2. Definition of Subgroups

In the study protocol, the following subgroups of patients are defined for this trial:

- Gender (male patients; female patients)
- Age of patient (below or equal to median; above median)  
Patients will be grouped for each analysis population separately
- Age of patient (4 subgroups according to the quartiles (values up to quartile))  
Patients will be grouped for each analysis population separately
- Degree of SSHL (PTA summary value at Screening >30 dB; ≤ 30 dB)
- Duration of SSHL before start of treatment (below or equal to median; above median)  
For the computation of SSHL duration, see Section 4.3; patients will be grouped for each analysis population separately
- SSHL with / without associated vestibular symptoms (spontaneous nystagmus; no spontaneous nystagmus beats) at Screening
- Presence of tinnitus (tinnitus; no tinnitus)  
If at Screening the answer to the question "Occurrence of Tinnitus?" is 'Yes', the patient will be categorized into the subgroup 'Tinnitus'
- Status of the contralateral ear at Screening (as mean of hearing loss in the frequencies 500 Hz, 1 kHz, 2 kHz, and 4 kHz):
  - 0 – normal hearing (25 dB or better)
  - 1 – mild hearing loss (>25 to 40 dB)

- 2 – moderate hearing loss (>40 to 60 dB)
- 3 – severe hearing loss (>60 to 80 dB)
- Baseline fibrinogen level ( $\leq 360$  mg/dL;  $> 360$  mg/dL)  
For the computation of the baseline fibrinogen level, see Section 4.3
- Baseline fibrinogen level (4 subgroups according to the quartiles (values up to quartile))  
For the computation of the baseline fibrinogen level, see Section 4.3; patients will be grouped for each analysis population separately
- Use of rescue medication (yes; no)  
For the identification of rescue medication, see Section 8.3
- Isolated low and/or high frequency sensorineural hearing loss (PTA air):
  - With/without isolated hearing loss at the low frequencies 125 Hz, 250 Hz, or 500 Hz
  - With/without isolated hearing loss at the high frequencies 4 kHz, 6 kHz, or 8 kHz
  - With/without isolated hearing loss at the low and high frequencies.

The statistical analysis of subgroups is addressed in Section 5.7.

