#### 9.2.5. Biomarkers

The following biomarkers are determined at Screening (Visit 1) and Day 8 (Visit 5) in venous blood samples as surrogate parameters for efficacy:

- Inflammatory markers: interleukin-6, TNF- $\alpha$
- Molecular markers of leucocyte activation: CD38+, CD40+ cells.

The change in biomarkers from Screening to Day 8 will be analyzed for the FAS in analogy to the primary efficacy variable, excluding the categorical analysis, the multiple linear regression, and the subgroup analyses.

Moreover, the inflammatory and cellular markers' relative change at Visit 5 will be correlated (Spearman's correlation coefficient) with the following effects:

- PTA (Air) absolute change at Visit 5
- Fibrinogen relative change at Visit 5.

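### The step-down risk-factor model in SAP 5.7 starts with about 22 to 33 parameters for little more than 30 patients, and with no true predictor it would keep at least one false factor more often than not

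*Combined protocol and SAP*

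**What the plan says.** SAP 5.7 states that "a step-down analysis of covariance (ANCOVA) model will be established on above study variable that initially includes the subgroups" of SAP 4.2, leaving out the quartile and rescue-medication subgroups. It adds four biomarkers, the four-level SSHL type, diabetes mellitus, hypertension and ischemic heart disease, all at Visit 1. Every variable with p above 0.5 is removed in one step. After that, "successively the factor with lowest influence will be eliminated until a model remains that contains only the significant influence factors", with significance set at 0.05.

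Four other places bear on this:

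- SAP 2 drops the interim analysis, planned at 30 evaluable patients, because "in total only a few more evaluable patients will be enrolled than planned for the interim analysis".
- SAP 5.1 and 5.2 analyse quantitative efficacy variables by ANCOVA in PROC GLM, with treatment, centre (called random) and baseline value. SAP 3.3 reports eight actively enrolling sites, and SAP 5.5 allows centres to be pooled at the blind data review meeting.
- SAP 5.6 makes no multiplicity adjustment. Only the primary variable is tested confirmatorily.
- SAP 5.7 lists CD38+ and CD42+ cells among the biomarkers, whereas SAP 9.2.5 has "Molecular markers of leucocyte activation: CD38+, CD40+ cells", as does protocol 8.2.1.

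**The concern.** The SAP adapts the interim plan to the low recruitment but leaves the step-down model as it would be for a much larger trial. A model with nearly as many parameters as patients has few or no residual degrees of freedom. Its p-values are then very unstable or do not exist, and the first elimination step has nothing to work on. The SAP gives no fallback for that case.

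Separately, choosing among many factors by unadjusted p-values produces false findings at any sample size. The result goes into Table 14.2.1.6, whose title says that it identifies risk factors, so a reader of the study report could take noise for predictors of hearing recovery. The relation of biomarkers to efficacy is a stated secondary objective, so a spurious biomarker finding could carry weight in later planning.

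**Working it through.** **The plan's own figure.** SAP 3.5 uses "2-sided t-tests with a global alpha level of 5 % and a statistical power of 90" per cent, to "confirm a treatment difference of 15 dB PTA of active treatment versus placebo with a 2:1 randomization". It adds: "A standard deviation of 20 dB for the test statistic is assumed". Placebo n = (1 + 1/2) × (1.960 + 1.282)² × 20² / 15² = 1.5 × 10.51 × 1.778 = 28.02, rounded up to 29. The ancrod group is then 58 and the total 87 (exact t-test power 0.903). With the 12% dropout of SAP 5.3, 87 / 0.88 = 98.9, so 99. Both figures reproduce. The documents give no parameter count or error rate for the step-down model.

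**Parameter count** (SAP 4.2, 5.2, 5.7, 3.3).

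- Gender, age at the median, degree of SSHL, duration, vestibular symptoms, tinnitus, fibrinogen at 360 mg/dL: 7 × 1 = 7
- Contralateral ear, four levels: 3
- Isolated low, high, and low-and-high frequency loss: 3 (1 if coded as one indicator)
- Biomarkers, continuous: 4
- SSHL type, four levels: 3
- Three comorbidities: 3

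Candidates: 7 + 3 + 3 + 4 + 3 + 3 = 23. Adding intercept, treatment and baseline PTA gives 26. Seven terms for eight unpooled centres give 33. The narrowest reading (isolated loss as 1, candidates and intercept only) gives 21 + 1 = 22.

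**Residual degrees of freedom, n minus parameters.** The SAP gives no final number, so 30 to 40 is an assumption.

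| n | 22 parameters | 26 parameters | 33 parameters |
|---|---|---|---|
| 30 | 8 | 4 | -3 |
| 33 | 11 | 7 | 0 |
| 36 | 14 | 10 | 3 |
| 40 | 18 | 14 | 7 |
| 87 | 65 | 61 | 54 |

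**False selections.** There are 8 subgroup factors, 1 or 3 for isolated loss, 4 biomarkers, 1 for SSHL type and 3 comorbidities, so 17 to 19 factors. If each were tested once, independently, at 5%, the chance of at least one false finding would be 1 − 0.95^17 = 58% to 1 − 0.95^19 = 62%.

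The two-step rule was then simulated with no true predictor. There were 1,200 data sets per setting, with partial F tests, any treatment, baseline and centre terms forced in, and centre as ordinary columns. Each cell gives the share of fitted data sets that kept at least one factor, then the mean number kept. The simulation standard error is about √(0.65 × 0.35 / 1,200) = 1.4 percentage points when all data sets are fitted.

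| n | 22 parameters | 26 parameters | 33 parameters |
|---|---|---|---|
| 30 | 65.7%; 2.01 | 65.7%; 2.88 | 99.8% could not be fitted |
| 33 | 64.2%; 1.73 | 64.7%; 2.31 | 39.3% could not be fitted; otherwise 55.1%; 4.16 |
| 36 | 65.1%; 1.66 | 67.5%; 2.07 | 60.1%; 2.78 |
| 40 | 63.1%; 1.46 | 68.6%; 1.85 | 67.7%; 2.16 |
| 87 | 62.2%; 1.05 | 63.9%; 1.17 | 66.9%; 1.26 |

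These runs took the factors as independent. A second set of 1,000 runs per setting used correlated and overlapping factors. It assumed, for example, hypertension in 40%, diabetes in 15%, ischemic heart disease in 8% and tinnitus in 70%; none of these frequencies comes from the documents. At least one factor was kept in 56 to 66% of fitted data sets. The version with centres could not be fitted in 66% of data sets at n = 30. At n = 33 it could always be fitted, with 2.9 residual degrees of freedom on average.

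**The case against.** The strongest reply is that this is one exploratory table. SAP 5.1 and 5.6 confine confirmatory testing to the primary variable, and nothing in SAP 5.7 can change that test. This stands and limits the importance of the point.

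The second reply is that 33 is an upper bound. Centres may be pooled, empty or overlapping categories use no rank, and a true random centre effect would cost less. This also stands, except that PROC GLM fits centre as ordinary model columns, so calling it random in SAP 5.2 saves nothing. The full analysis set may exceed the evaluable number, but missing biomarkers or other baseline covariates would pull the usable number down again. The narrowest reading still leaves only 11 residual degrees of freedom at 33 patients.

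A reader might infer three stronger things that the documents do not support:

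- **Saturation as the main cause of false findings.** The rate is about as high at 87 patients (62 to 67%). Small n mainly raises the number of false factors kept and the risk that the model cannot be fitted.
- **Hardly any patient at or below 30 dB on the severity subgroup.** The subgroup is "Degree of SSHL (PTA summary value at Screening" above or at most 30 dB, an absolute value, whereas inclusion criterion 1 is relative to the other ear. With contralateral thresholds of 0 to 10 dB, a 20 dB difference at three consecutive frequencies gives 20 to 30 dB and qualifies. No baseline distribution is given, so a different cut cannot be justified on this ground.
- **Treatment eliminated from its own model.** SAP 5.2 puts treatment in these ANCOVA models, and SAP 5.7 names only subgroups and factors as candidates.

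**Conclusion.** The point holds. As written, SAP 5.7 fits about 23 candidate degrees of freedom to little more than 30 patients. If 30 to 40 patients are analysed, 4 to 18 residual degrees of freedom remain without centre. With eight unpooled centres there are few or none at 30 to 33 patients, where the p above 0.5 step may not be computable. With no true predictor, roughly 55 to 70% of fitted data sets would still yield at least one risk factor.

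These rates rest on assumed patient numbers and category frequencies and are best read as a range. They describe a global null; the documents do not show that none of the factors matters. The primary analysis is not affected. The CD42+ entry is a separate inconsistency and depends on no assumption.

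**What to change.** Before unblinding, delete the p-value elimination from SAP 5.7 and rely on the fixed multiple regression already planned in SAP 9.1.1 (Table 14.2.1.4):

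- State a closed list of terms: treatment, age, SSHL duration and baseline hearing loss, the last three preferably continuous. SAP 9.1.1 currently gives its covariates only as examples. With an intercept this is 5 parameters, leaving 33 − 5 = 28 residual degrees of freedom at 33 patients. Report estimates with 95% confidence intervals.
- Name the analysis set. SAP 9.1.1 speaks of patients who completed the study, while Table 14.2.1.4 is listed for the full analysis and per protocol sets.
- Show the remaining factors only descriptively, labelled hypothesis-generating. Protocol 10.2.1 wants the effect of diabetes, hypertension and ischemic heart disease included, and neither these nor the biomarkers are among the SAP 4.2 subgroups, so rows for them must be added.
- Remove or retitle Table 14.2.1.6.
- Correct CD42+ in SAP 5.7 to CD40+.

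The cost is SAP wording, a few descriptive rows and less model programming. The downside is that fewer factors are examined jointly.
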